**Behavioral, mental health, and alcohol use measures**			
	Demographics	Items developed for previous Suubi studies [72-74], including age, sex, parents’ occupation, household size, orphanhood status, primary caregiver, and community of origin	Baseline
	COVID-19 experiences	CASPE^a^ (adapted from Suubi+Adherence [74] and the study by Ladouceur [75])	Baseline
	HIV testing	Self-report of HIV test (yes/no; past year [at baseline], during the study period [immediately after the intervention], and past 3 months [at follow-up]) confirmed with proof of results from the clinic using measures and procedures adapted from Suubi studies [72-74]	Baseline, immediately after the intervention, and 3-month follow-up
	Intention to test for HIV	Questions adapted from a study of secondary school students in Uganda [76]	Baseline, immediately after the intervention, and 3-month follow-up
	Self-efficacy	Questions adapted from a study with secondary school students in Uganda [76] and a study with high school students in the United States [77], including questions regarding self-efficacy in testing for HIV, trying PrEP^b^, using condoms consistently, contacting a behavioral health counselor	Baseline, immediately after the intervention, and 3-month follow-up
	Current HIV prevention strategies	This measure includes items developed for previous Suubi studies [72,73] in Uganda (in addition to a question regarding PrEP; range 5-25; 5 question items; α=.70), for example, “I think it is very important to use condoms every time one has sex,” “as a teenager I think AIDS is a threat to my health,” and “I think all people my age who have sex should use condoms.” Scores range from 4: strongly agree; 3: somewhat agree; 2: somewhat disagree; to 1: strongly disagree.	Baseline, immediately after the intervention, and 3-month follow-up
	HIV-related knowledge	This measure includes items from previous Suubi studies [72,73] in Uganda; this measure includes 13 items about HIV infection and prevention mechanisms (range 0-16; 16 question items; α=.83), for example, “HIV can be passed by an infected person even though that person is not feeling sick.” Possible scores are 1: true; 2: false; and 3: don't know or 1: not sure; 2: unsafe; and 3: safe.	Baseline, immediately after the intervention, and 3-month follow-up

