Most adolescents preferred SMS text messaging. Thus, to streamline our delivery, recruitment, and evaluation, we decided to focus on SMS text messaging in this pilot RCT. In addition, to protect privacy, we added an initial message to be sent on each day of the intervention period that asked, “is this a good time to chat?” By contrast, the initial prompt from the pilot test immediately introduced the topic of the day (HIV testing, mood, etc). If adolescents respond with “yes,” then they would be sent the follow-up message that introduces the topic of the week. If adolescents respond with “no,” they would be sent a message that says, “ok thanks, write back with yes when you are free and available.”In the pretest, adolescents who screened positive for symptoms of depression, anxiety, or hazardous alcohol were provided with the contact number of the general StrongMinds counselor. As described earlier, adolescents expressed concern that they would incur charges by calling StrongMinds counselors. Therefore, we revised our methods (including language in our consent forms), and in the RCT, we will provide a daily update to StrongMinds counselors with a list of contact numbers of adolescents who screened positive for symptoms of depression, anxiety, or hazardous alcohol use.On the basis of our initial focus group discussions and our presentation at the HIV Implementation Science Fellowship, we expect that a 3-month follow-up will be sufficient to determine feasibility and accessibility. In addition, a shorter follow-up period will limit the possibility of unforeseen historical or COVID-19–related interruptions.

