### Statistical Analysis

#### Primary and Secondary Outcomes and Analysis

Summary statistics will be used to describe all metrics and compare them between the students receiving Kirabo and those in usual care at baseline, 1-month postintervention assessment, and the final 3-month follow-up assessment. Means and SDs will be used for continuous outcomes, followed by box plots, and frequency tables will be used for binary and categorical metrics. The primary analysis of this RCT will test whether postintervention HIV testing rates among the adolescents who interacted with Kirabo are significantly higher than those who received standard of care. We will use a generalized linear mixed model to determine statistical significance. In the model, the outcome is the binary indicator of whether an adolescent received an HIV test during or immediately after the intervention. We will also examine the differences between the model at the 3-month follow-up. The main predictor is the intervention assignment (Kirabo or usual care). The school will be included in the model as the random effect to adjust for within-school correlations. We will apply similar analyses to investigate the impact of Kirabo on the secondary outcomes.

Depending on the nature of the outcome, we will use different link functions in the generalized linear mixed model. We will use the identity link for continuous outcomes, the logistic link for binary outcomes, and the log function for ordinal outcomes. For incidence/frequency outcomes, a log function with adjustment for exposure time will be used. We will formally test whether the students in the 2 intervention groups have comparable baseline characteristics, including demographic factors, moderators, and variables measuring potential mechanisms of action (Table 2). If any of these variables are significantly different at baseline, they will be included in the model to adjust for their potential confounding effects.

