#### Primary End Point Analysis for the Pilot RCT

We will recruit 200 students who own mobile phones and randomize them in a 1:1 ratio into intervention and control groups. The variables of focus are listed in Table 2. The primary end point is the binary indicator of whether there is an increase in HIV testing following the intervention. Chi-square tests will be used to determine whether intervention participants were more likely to take an HIV test in the past month. We will then build a logistic model to estimate intervention efficiency while adjusting for baseline characteristics, including baseline HIV prevention strategies, HIV knowledge, sexual risk behaviors, depression, anxiety, alcohol use, and demographics. The same analysis will be applied to the 6-month postintervention follow-up to determine the long-term effects of the intervention. These estimated parameters allow reliable estimates of sample size, power, and detectable effects for the subsequent study.

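### The primary HIV-testing analysis is specified twice, with different tests, outcome windows and covariate rules, and one version is repeated at a 6-month follow-up that is not in the schedule

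*Protocol article*

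**What the plan says.** Two sections of the protocol article each present a primary analysis of HIV testing.

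- **Primary and Secondary Outcomes and Analysis.** On the primary comparison: "We will use a generalized linear mixed model to determine statistical significance". On clustering: "The school will be included in the model as the random effect to adjust for within-school correlations". On covariates: "If any of these variables are significantly different at baseline, they will be included in the model". The outcome is a yes/no indicator of a test during the intervention or directly after it, with a further look at 3 months. The same section lists the assessments after baseline as a "1-month postintervention assessment, and the final 3-month follow-up assessment".
- **Primary End Point Analysis for the Pilot RCT.** "Chi-square tests will be used to determine whether intervention participants were more likely to take an HIV test in the past month". A logistic model follows, with a fixed list of baseline covariates and no mention of school. Then: "The same analysis will be applied to the 6-month postintervention follow-up to determine the long-term effects of the intervention". The end point itself is worded as an indicator of an increase in testing.

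The schedule is given elsewhere. Measures (Overview) lists three main time points: baseline, immediate postintervention and 3 months. Phases 5 to 6 records that 6 months was the initial plan and then adopts the shorter period: "we expect that a 3-month follow-up will be sufficient to determine feasibility and accessibility". In Table 2, the HIV-testing item asks about the past year at baseline and, after that, about tests "during the study period [immediately after the intervention], and past 3 months [at follow-up".

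**The concern.** A single primary result needs one test, one outcome window, one covariate rule and one set of time points. Here each is stated twice and differently, and neither section is called a sensitivity analysis. Whoever analyses the data could report either result as primary and still be following the protocol. Measures (Overview) names HIV testing as the primary outcome, and Primary End Point Analysis says its estimates will size the next study, so it matters which one is carried forward.

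Two further problems follow. The 6-month analysis refers to a visit that the trial does not hold. And the recall window at the 3-month visit, as worded, may leave out tests taken during the intervention, so that visit may not show the cumulative effect on testing.

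**Working it through.** **1. Does the power statement settle which test is primary?** Effectiveness Power Analysis gives 26% against 46%, 100 per arm, 80% power, alpha 0.05. For two independent proportions, two-sided, with mean proportion 0.36:

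n = [1.960 × √(2 × 0.36 × 0.64) + 0.842 × √(0.26 × 0.74 + 0.46 × 0.54)]² / 0.20² = (1.330 + 0.559)² / 0.04 ≈ 89.2, so 90 per arm.

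With continuity correction: (89.2 / 4) × [1 + √(1 + 4 / (89.2 × 0.20))]² ≈ 99 per arm, against 100 stated. Fisher's exact test at 100 per arm has 80.4% power; the uncorrected formula gives 84.3%. The figure therefore reproduces as a simple two-proportion comparison. A design effect of about 1.12 would also bring the uncorrected formula to 80%, and no intraclass correlation is stated. The power statement fits either analysis and does not choose between them.

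**2. The two specifications side by side.**

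| Element | Primary and Secondary Outcomes and Analysis | Primary End Point Analysis |
|---|---|---|
| Test | Mixed model | Chi-square, then logistic model |
| School | Random effect | Not stated |
| Covariates | Only if significantly imbalanced | Fixed list |
| Outcome window | During or just after the intervention | Past month |
| Later time point | 3 months | 6 months |

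All five rows differ.

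**3. Schedule.** Measures (Overview), Table 2, Procedures, Phases 5 to 6 and Secondary End Point Analysis all have 3 months as the only later follow-up. The 6-month reference matches the plan that Phases 5 to 6 says was replaced, and appears to be left over from it.

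**4. Outcome window.** Table 2 has no past-month item; its postintervention item covers the study period. The intervention lasts 5 weeks (Accessing Kirabo), so a one-month recall at its end covers about 30/35 = 86% of it. If testing were constant at the 26% 12-month rate (an assumption), the expected proportion tested is 1 − 0.74^(1/12) = 2.5% in one month and 1 − 0.74^(35/365) = 2.8% in 5 weeks. The gap is small. It would be large only if the 1-month postintervention assessment is a separate visit a month after the intervention ends. A past-month recall there would cover none of the intervention.

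**5. The 3-month item (secondary point).** Secondary End Point Analysis places this visit 3 months after the intervention. A 3-month recall then begins at about the end of the intervention. Suppose that proportions a and b of the two arms tested during the intervention, and that later testing rates are the same in both arms: r1 among those already tested, r0 among the rest. The past-3-months difference is (a − b) × (r1 − r0), which is negative whenever a > b and r1 < r0.

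Illustration with assumed inputs a = 0.46, b = 0.26, r0 = 0.10:

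- r1 = 0: 0.54 × 0.10 = 5.4% against 0.74 × 0.10 = 7.4%, a difference of −2 points. Any test since randomization: 0.46 + 0.054 = 51.4% against 0.26 + 0.074 = 33.4%, a difference of +18 points.
- r1 = 0.05: 0.023 + 0.054 = 7.7% against 0.013 + 0.074 = 8.7%, a difference of −1 point.
- r1 = 0.10: no difference.

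The reversal also needs the effect to stop at week 5. With r1 = 0, the arms are level once untested Kirabo students test at 0.074 / 0.54 = 13.7% instead of 10%; with retesting at half the rate, at 0.087 / 0.77 = 11.3%.

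**The case against.** The strongest reply is that this is a pilot. Acceptability Power Analyses gives acceptability and feasibility as its main purpose, the efficacy estimates are called preliminary, the 6-month phrase is a visible leftover, and past month is probably shorthand for the 5-week period. That lowers the stakes and explains how the text arose. It does not say which test is primary.

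Four stronger readings are tempting, and the documents do not support them.

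- **That the 3-month outcome will reverse a real effect.** The illustration uses a 12-month rate (26%) as if it were a 5-week rate, assumes no lasting effect and assumes less retesting by earlier testers. None of this is in the protocol. Testing in the 3 months after a programme is also a legitimate persistence question, and tests during the intervention are recorded at the earlier visit.
- **That the follow-up item certainly misses the intervention.** This rests on the timing in Secondary End Point Analysis. The timeline figure is not available here; if the 3 months ran from baseline, the recall would cover most or all of the intervention.
- **That the chi-square test inflates false positives.** Individuals are randomized within school and gender strata (Procedures). Ignoring prognostic strata then generally makes the test conservative. The mixed model has no stated gender term either.
- **That the increase wording defines a change within each person.** The text does not say so, and the next sentence compares the arms on taking a test. It is loose wording.

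**Conclusion.** The concern holds as an internal contradiction. The protocol states two unranked primary analyses of HIV testing that differ in test, handling of school, covariate rule, outcome window and later time point, and one of them cannot be completed because there is no 6-month visit. This rests only on current text and needs no assumption. Its size is two competing primary results; no bias in either one is claimed. The past-month discrepancy alone is minor, about 5 of 35 days.

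The 3-month recall window is a secondary point and is conditional. If the visit is timed from the end of the intervention, earlier testers retest less often and the effect does not persist, the past-3-months comparison could understate or reverse the arm difference. The 5.4% against 7.4% figures show only that this is possible.

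**What to change.** 1. Name one primary analysis: the logistic mixed model in Primary and Secondary Outcomes and Analysis, with school and also gender (the other randomization stratum), in all randomized participants. This agrees with the intention-to-treat approach in Handling of Missing Data.
2. In Primary End Point Analysis, label the chi-square test and the separate logistic model as sensitivity analyses, or delete them. State one covariate rule for the primary model.
3. Define the primary outcome as any HIV test from randomization to the immediate postintervention assessment, using the Table 2 study-period item. Use this in place of the past-month and increase wording.
4. Change the 6-month reference to 3 months, and reconcile the 1-month postintervention assessment with the immediate one.
5. State whether the 3-month visit is timed from baseline or from the end of the intervention. At that visit, report any test since randomization by combining the two postbaseline Table 2 answers, and keep the past-3-months rate as a descriptive outcome.

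The cost is protocol wording. Both items needed are already in Table 2, so no new data collection is required. Results says that no data had been analyzed at submission. The change should be fixed and dated before any outcome comparison by arm.

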#### Effectiveness Power Analysis

There is limited information on the impact of SMS text message–based interventions on increasing HIV testing among adolescents in rural Uganda. We expect that the baseline 12-month HIV testing rate among adolescents aged 15 to 19 years will be 26% [97]. With 200 students (intervention: n=100, 50%; standard of care: n=100, 50%) from 10 schools, we have 80% power to detect an average postintervention HIV test rate of ≥46% at the significance level of.05.

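### The adjusted logistic model carries six scales plus demographics on about 72 expected events; fitted by ordinary maximum likelihood, a true effect would be overstated by about 10% on the log-odds scale, or more if items are dummy-coded

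*Protocol article*

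**What the plan says.** The section Primary End Point Analysis for the Pilot RCT sets out two steps. A chi-square test first asks "whether intervention participants were more likely to take an HIV test in the past month". The section continues: "We will then build a logistic model to estimate intervention efficiency", and this is to be done "while adjusting for baseline characteristics, including baseline HIV prevention strategies, HIV knowledge, sexual risk behaviors, depression, anxiety, alcohol use, and demographics". It gives no limit on the number of covariates, no coding, and no estimation method beyond calling the model logistic. It closes by saying that the resulting parameters will be dependable inputs for sizing the next study.

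Table 2 describes the demographic block as items "including age, sex, parents’ occupation, household size, orphanhood status, primary caregiver, and community of origin".

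On size, the plan says: "We will recruit 200 students who own mobile phones and randomize them in a 1:1 ratio into intervention and control groups". Effectiveness Power Analysis takes 26% as the expected 12-month testing rate and states that "we have 80% power to detect an average postintervention HIV test rate of ≥46% at the significance level of.05".

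A different model appears under Primary and Secondary Outcomes and Analysis. There the primary analysis is a generalized linear mixed model with assignment as main predictor and school as random effect. It adds only those baseline variables that differ significantly between arms.

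**The concern.** Maximum-likelihood logistic regression has a known small-sample fault. When events are few relative to the number of coefficients, non-zero coefficients are estimated too far from zero and model-based standard errors are too small. The article names six scales and a demographic block for a trial of 200 students with a binary outcome, and says the output will support planning of the next trial. An effect that is systematically overstated would make a trial sized on that odds ratio too small, and an interval with less than its stated coverage would hide part of the uncertainty.

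**Working it through.** **The plan's own figure.** With p1 = 0.26, p2 = 0.46, n = 100 per arm and two-sided alpha 0.05:
- standard error under the null: sqrt(2 × 0.36 × 0.64/100) = 0.0679
- standard error under the alternative: sqrt((0.26 × 0.74 + 0.46 × 0.54)/100) = 0.0664
- power without continuity correction: Φ((0.20 − 1.96 × 0.0679)/0.0664) = Φ(1.008) = 84.3%
- power with continuity correction (subtract 1/n = 0.01 from the difference): Φ(0.858) = 80.5%

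The stated 80% is therefore reproduced with the continuity correction, and the two rates can be used as inputs.

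**Events.** 100 × 0.26 + 100 × 0.46 = 72. If both arms are at 26%, the count is 52.

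**Parameters.** Six scales plus seven demographic items at one parameter each is 13, or 14 with treatment: 72/14 = 5.1 events per parameter. Occupation, orphanhood, caregiver and community could each take several dummy variables, but the coding is not given. The counts of 20, 26 and 30 below are assumptions.

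**Simulation.** 200 students, 1:1, marginal rates 26% and 46% (odds ratio 2.42, log odds ratio 0.886), ordinary maximum likelihood, 3,000 to 4,000 runs per setting. The covariates' linear predictor had a standard deviation between 0 and 1.0; the 3- and 8-parameter runs used 0.5. Bias is measured against the true conditional log odds ratio, so non-collapsibility is not counted as bias. The Monte Carlo standard error of coverage is about sqrt(0.95 × 0.05/3000) = 0.4 points.

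| Covariate parameters | Events per parameter (with treatment) | Bias of log odds ratio | 95% CI coverage |
|---|---|---|---|
| 3 (short list) | 72/4 = 18.0 | +3.1% | 94.8% |
| 8 (six scales, age, sex) | 72/9 = 8.0 | +6.7% (about 4–7% across simulations) | 94.9% |
| 13 (each item once) | 72/14 = 5.1 | +9 to 10% | 93.2–93.8% |
| 20 (assumed coding) | 72/21 = 3.4 | +13 to 16% | 92–93% |
| 26 (assumed coding) | 72/27 = 2.7 | +18 to 22% | 91–92% |
| 30 (assumed coding) | 72/31 = 2.3 | +22 to 24% | about 90% |

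The mean model-based standard error is 4–6% below the empirical standard deviation at 13 parameters and about 10% below it at 30.

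**Other conditions.**
- No effect (26% in both arms): the mean log odds ratio is −0.008, 0.001 and −0.014 at 13, 20 and 26 parameters, so there is no inflation. Coverage is 93.8%, 95.0% and 93.6%.
- Smaller effect (26% and 36%), 13 parameters: bias +9.8%, coverage 94.0%. The proportional bias does not depend on reaching 46%.
- Lower rates (assumed 10% and 25%, 35 events): bias +12% at 13 parameters and +27% at 26. This matters because 26% is a 12-month rate while the outcome in this section covers the past month.

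**Firth penalisation** at 26% and 46% (2,000 runs): bias +0.8% with coverage 96.4% at 13 parameters; bias +2.4% with coverage 95.4% at 26.

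**Planning consequence, if the next trial is sized on this log odds ratio.** Required n is proportional to 1/(log odds ratio)². A 10% inflation gives 1/1.10² = 0.83, about 17% too few students; 24% gives 1/1.24² = 0.65, about 35% too few.

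**The case against.** The strongest reply is that the article does not fix the model tightly enough to fix the bias. It says only demographics; the seven items in Table 2 describe a questionnaire block, not a model statement, and the section on secondary end points names just age, gender and unspecified others. Coding, the final covariate list and the fitting method are commonly left to an analysis plan. This stands, and it is why the size can only be given as a range with its assumptions. A reader might infer that the odds ratio will be inflated by up to a quarter and that its interval is plainly too narrow. The document does not support that: the upper end needs many dummy variables, the inflation needs a true effect, and the undercoverage at 13 parameters is slight.

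A reader might also infer that the model will often fail to fit. That came only from the most extreme case tried: 32 covariate parameters at assumed rates of 10% and 20%. At 10% and 25% with 26 parameters no fit failed in 4,000 runs.

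Sampling error is also much larger than the bias. The unadjusted log odds ratio has standard error sqrt(1/26 + 1/74 + 1/46 + 1/54) = 0.304, giving an interval of about 0.29 to 1.48; a 10% bias (0.09) is under a third of one standard error. This is fair, but sampling error goes either way, whereas this bias has one direction and can be avoided.

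It can be said too that the next trial need not be sized on the adjusted odds ratio. The article's own sizing uses two proportions, which this bias does not touch, and the sentence about planning follows both the chi-square test and the model. So the 17% and 35% shortfalls are conditional.

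Finally, the mixed model is what the article calls the primary analysis, and it does not carry this list. That limits the reach of the point, but the model discussed here is the one introduced to estimate the effect, and the article does not say which result prevails.

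**Conclusion.** The point holds in a conditional form. At the plan's own rates, entering every listed item once gives about 5 events per parameter. Ordinary maximum likelihood would then overstate a true log odds ratio by about 10%, with 95% interval coverage of about 93–94%. With 26 to 30 parameters, an assumption about category coding, the overstatement is about 20–24% and coverage about 90–92%. With only age and sex as demographics it is about 4–7% and coverage is nominal. With no true effect the estimate is not inflated. Past-month testing below the 12-month rate would mean fewer events and somewhat more bias. This is a moderate, avoidable weakness in an estimate meant to inform the next trial. It does not undermine the trial, the chi-square comparison or the arm proportions.

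**What to change.** Either of two changes to Primary End Point Analysis for the Pilot RCT is enough:

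- Keep the covariates and state that the model is fitted with Firth's penalised likelihood (simulated bias about 0–2%, coverage about 95–96%).
- Or restrict the model to a short pre-specified covariate list, with the number of parameters stated, and keep the full list as a sensitivity analysis.

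In both cases, state how this model relates to the mixed model with a school random effect and which of the two supplies the reported effect. Base planning of the next trial on the penalised or short-list estimate, or on the arm proportions with their intervals.

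The cost is wording and a little more analysis work. If the list is shortened, some prognostic adjustment is lost from the main estimate. No change to recruitment, data collection or sample size is needed.
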